The go/no-go task assessed inhibitory control in young children [44-48]. In our study, we used an app-based version of the go/no-go task on an Apple iPad. Children were tasked with catching fish (go trials) and avoiding sharks (no-go trials) as they moved across the screen [49]. To enhance the dominant response and increase the difficulty of inhibiting responses during the “no-go” trials, 80% (n=60) of the trials were “go” trials and 20% (n=15) were “no-go” trials. Before starting, children received instructions on both trial types and practiced 5 trials of each. This was followed by a mixed block of 10 practice trials (with 80% being “go” trials). A brief review of the instructions was provided before the task began. The main task consisted of 75 test stimuli evenly distributed across 3 blocks. The stimuli were presented in pseudorandom order, ensuring that no block began with a “no-go” trial and that no more than 2 consecutive “no-go” trials occurred. A 1000-millisecond interval was maintained between stimuli. Scores were calculated by first excluding trials with response times <300 millisecond, as these were considered non–task related. Next, blocks were removed if the child demonstrated nonresponsiveness (ie, go trials with <20% accuracy or no-go trials with >80% accuracy) or indiscriminate responding (ie, go trials with >20% accuracy and no-go trials with <20%). The impulse control score, which reflects the ability to withhold a response in the presence of a strong, automatic tendency to respond, was calculated by multiplying the percentage of correct “go” responses by the percentage of correct “no-go” responses.

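### The go/no-go exclusion for indiscriminate responding does not require a high go response rate, so blocks of plain failed inhibition are deleted instead of counted as zero

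*Protocol article*

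**What the plan says.** The go/no-go paragraph under Behavioral Assessments sets out the task and its scoring. "80% (n=60) of the trials were" go trials and the other 15 were no-go trials. "The main task consisted of 75 test stimuli evenly distributed across 3 blocks".

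Scoring has three steps:

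1. Trials with responses faster than 300 ms are dropped.
2. Whole blocks are removed under two clauses. For nonresponsiveness, "blocks were removed if the child demonstrated nonresponsiveness (ie, go trials with <20% accuracy or no-go trials with >80% accuracy". The second clause is "indiscriminate responding (ie, go trials with >20% accuracy and no-go trials with <20"%.
3. Percentage correct on go trials is multiplied by percentage correct on no-go trials. The result is described thus: "The impulse control score, which reflects the ability to withhold a response in the presence of a strong, automatic tendency to respond".

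**The concern.** Indiscriminate responding means tapping at everything, which shows as high go accuracy together with very low no-go accuracy. The printed go condition does not ask for high go accuracy. It asks only that the block is not one already caught by go below 20%. A test with two parts therefore becomes a test on no-go accuracy alone, and no-go accuracy is half of the score itself.

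Failing to withhold a response is what the score is meant to measure. If blocks showing that failure are removed, children with weak inhibition are scored on their better blocks only, and some may have no score. The low end of the scale is cut according to the outcome.

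**Working it through.** **Inputs from the article.** 60 + 15 = 75 trials; 60/75 = 80% go; 75/3 = 25 stimuli per block. These figures agree with one another.

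**Assumptions.** 60/3 = 20 go and 15/3 = 5 no-go trials per block (the article says the stimuli are split evenly, not the trial types). Trials are independent. The nonresponsiveness clause is left out so that this clause is seen alone. True accuracies are scenarios, because the article reports none.

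**Step 1: what no-go below 20% means.** 1/5 = 20% is not below 20%, so the condition is 0/5. If the 300 ms filter leaves 1 to 4 no-go trials, it still means none correct. With 6 no-go trials in a block, 1/6 = 16.7% would be caught too.

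**Step 2: what go above 20% means.** At least 5/20. The probability of meeting it is 0.949 at true go accuracy 40%, 0.994 at 50% and about 1 at 70%. Blocks with 3/20 or fewer are removed by the other clause. A 0/5 no-go block survives only at exactly 4/20 go.

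So 14/20 go with 0/5 no-go is removed, and so is 5/20 go with 0/5 no-go. Neither child tapped at everything.

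**Step 3: share of blocks deleted.** With true go accuracy p and no-go accuracy q, d = P(go count ≥ c) × (1 − q)^5, where c = 5 as printed and c = 17 for a cut-off above 80%.

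- 70%/20%: printed 1.000 × 0.328 = 0.328; above 80%, 0.107 × 0.328 = 0.035.
- 90%/20%: printed 1.000 × 0.328 = 0.328; above 80%, 0.867 × 0.328 = 0.284.

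**Step 4: mean score.** Every deleted block has product 0, so the mean block score among retained blocks is 100pq/(1 − d).

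- 70%/20%: no removal 14.0; printed 14.0/0.672 = 20.8; above 80%, 14.0/0.965 = 14.5.
- 90%/20%: no removal 18.0; printed 18.0/0.672 = 26.8; above 80%, 18.0/0.716 = 25.1.

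The article does not say how retained blocks are combined. A simulation of 200,000 children with three blocks each, pooling the percentages over retained blocks, gives 14.4 and 25.0 for the two above-80% values and leaves the printed values unchanged. The table uses pooled percentages.

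| True go / no-go | No removal | Printed: blocks deleted, score | Above 80%: blocks deleted, score |
|---|---|---|---|
| 70% / 10% | 7.0 | 59%, 17.1 | 6%, 7.4 |
| 70% / 20% | 14.0 | 33%, 20.8 | 3.5%, 14.4 |
| 70% / 30% | 21.0 | 17%, 25.3 | 2%, 21.3 |
| 90% / 10% | 9.0 | 59%, 22.0 | 51%, 18.4 |
| 90% / 20% | 18.0 | 33%, 26.8 | 28%, 25.0 |
| 90% / 30% | 27.0 | 17%, 32.4 | 15%, 31.6 |

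**Step 5: children with no score.** Under the printed rule the chance of losing all three blocks is about (1 − q)^15: 0.9^15 = 21% at no-go 10%, and 0.8^15 = 3.5% at no-go 20%. With the cut-off above 80% and no-go 10%, it is about 0% at go 70% and 13.4% at go 90%.

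**One child by hand.** Go 14/20 in every block; no-go 0/5, 0/5 and 2/5. All blocks: 0.70 × 2/15 = 9.3%. Printed rule, one block left: 0.70 × 2/5 = 28%. With the cut-off above 80% all three blocks stay and the score is 9.3%.

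**The case against.** **The printed clause can be read coherently.** Go below 20% marks a child who is not responding, go above 20% one who is, and no-go below 20% then marks failure to discriminate. The article does not state 80%, and its scoring sources are not at hand. This stands in part: the 80% figure is inferred from the 20%/80% pair in the neighbouring clause, and the script may already use it. But on this reading the go condition still cannot separate tapping at everything from weak inhibition.

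**Some of the blocks are poor data.** A child at 5/20 go and 0/5 no-go taps a quarter of the fish and all the sharks, which may be a misunderstood rule. Excluding such a block can be defended, and keeping it is a real cost of the change. It is nevertheless not indiscriminate responding.

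**Much of the inflation comes from the no-go cut-off, which the change keeps.** This stands. At 90%/20%, (25.1 − 18.0)/(26.8 − 18.0) = 81% of the inflation remains. The task was built to strengthen the go response, so high go accuracy may be common. A reader might infer that >20% is the sole cause and that correcting it cures the bias; the figures do not support that.

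**Harm to the trial comparison is not shown.** This also stands. A reader might infer that the rule favours one arm, since control children are younger (mean 3.9 against 4.6 years), or that it hides improvement where improvement is likeliest. The article gives no task data by age, arm or level of performance, so a difference between arms is possible and no more.

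**The stakes are modest.** This is one of four behavioral tasks in a 32-child pilot, and the article does not name the score as a primary endpoint.

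**Conclusion.** The point holds as a fault in a stated scoring rule. The go condition is nearly vacuous as printed, and essentially every block with no correct no-go trial is deleted. For children with moderate go accuracy this matters: at 70%/20% the mean score is 20.8 against 14.0 with no removal (20.8/14.0 = 1.49, or 49% too high), and a cut-off above 80% brings it to about 14.4. For children with high go accuracy the choice of go cut-off makes little difference, and most of the inflation stays.

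The sizes rest on 5 no-go trials per block, independent trials and assumed accuracies, so they are a range and not an estimate for this sample. The article does not show that any score has actually been computed with >20%, which may be a misprint. It should be corrected, but it does not by itself undermine the pilot.

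**What to change.** 1. Check which go threshold the scoring script uses.
2. Change the clause to go accuracy above 80% and no-go accuracy below 20%, the mirror of the cut-offs in the nonresponsiveness clause. If the script used >20%, rescore the stored trials; if it did not, correct the article only.
3. Report the number of blocks and of children removed in each arm under each clause.
4. Add a sensitivity score in which no block is removed for 0/5 no-go, because the corrected clause still cuts the low end for children with high go accuracy.

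The cost is one threshold, a rerun on stored app data and a short table. The article says data are still being processed, so this can be done before analysis. The downside is that a few low-quality blocks are kept and count as zero no-go accuracy.

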#### Biomarkers

##### Overview

Data were collected to assess potential physiological mechanisms driving the intervention effects. These mechanisms were evaluated across several biological systems: the autonomic nervous system, the hypothalamic-pituitary-adrenal (HPA) axis, and the hypothalamic-pituitary-gonadal (HPG) axis. These systems were chosen because they play key roles in self-regulation and the body’s response to stress and challenge or threat [50].

##### HRV Measurement

HRV assesses acute stress response and reflects the balance between the sympathetic nervous system and parasympathetic nervous system, both of which are integral to maintaining homeostasis [51]. HRV is a well-established biomarker of an individual’s ability to regulate and recover from stress [52].

For teachers and children who opted into this component of data collection, HRV data were collected at multiple time points: before the intervention, every 4 weeks during implementation (with each new module), and at postintervention and 2-month follow-up assessments. To collect HRV data, trained research assistants attached Firstbeat Body Guard sensors (Firstbeat Technologies Ltd [53]) to the participants—both children and teachers—by placing them beneath the right collarbone and connecting the sensor cable to the rib cage on the opposite side [54]. If a participant had sensitivities to its placement on the front of the body, electrodes were placed in these equivalent locations on the back. The sensors were removed once data collection was complete.

##### HRV Collected During Implementation

For children, the baseline HRV was measured while they were sitting still or engaged in low-physical movement during class activities for approximately 3 to 5 minutes. During each program module, HRV was measured in both the active and recovery states, with sensors worn for around 20 minutes during the program implementation days. Teachers wore the sensors at the same time points as the children, both before and after the program, during normal classroom activities, and for the same amount of time as the children during the program.

##### HRV Collected During Behavioral Tasks

Children wore Firstbeat sensors while completing all the tasks, especially the gift delay task that was designed to induce moderate psychological stress. This task, commonly used in research to provoke a physiological stress response [55,56], was assessed via data collected at preintervention, postintervention, and 2-month follow-up time points. The task sequence involved 3 phases. First, there was a 3-minute baseline phase, where children colored quietly to establish a baseline HRV measurement. This was followed by a 3-minute gift delay task, which was intended to evoke the stress response. Finally, there was a 3-minute recovery phase, where children had time to recover after the stressor. Throughout the paradigm, heart rate and pulse wave activity were continuously monitored to assess changes in vagal tone, allowing for the measurement of both reactivity (the body’s immediate response to stress) and recovery (how well the body returns to baseline following stress). This procedure of baseline, task, and recover was followed for the pencil tapping, tower building, and go/no-go task as well, even though they were not hypothesized to elicit the same stress response as the gift delay task.

##### Hormone Measurements

Hair was collected to measure cortisol, testosterone, and dehydroepiandrosterone (DHEA) levels to capture chronic stress and threat-challenge exposure. Cortisol, a hormone secreted by the HPA axis, is known to rise in response to stress [57]. Testosterone, produced by the HPG axis, also increases in response to challenging situations [58,59]. DHEA is closely linked to both cortisol and testosterone and is needed to tease out the unique coupling effect. DHEA is produced adrenally in both the gonads and the brain. DHEA and its sulfated analog are the most abundant hormones in the body, and as an adrenal androgen, DHEA operates as an end-product of both HPA and HPG axes [60]. By examining the coupling of HPA and HPG axes activity, both independently and together, we can better predict the risk of negative health outcomes related to stress [61]. In addition, exploring HPA and HPG coupling broadens the understanding of stress from the traditional “fight-or-flight” response to a more nuanced “threat-challenge” framework, which can apply to a wider range of real-world stressors [58,62].

Hair samples were collected from both children and teachers who consented to participate in this component of the study. These samples were used to assess cortisol, DHEA, and testosterone levels, as hair is highly sensitive to hormonal changes. Hair sampling is more feasible than saliva collection in preschool-aged children, and hormone measurement is more reliable in hair than fingernail clippings. Hair samples were collected at 3 time points: preintervention, postintervention, and 2-month follow-up time points. A 1-cm section of hair reflects approximately 1 month of growth. Therefore, with hair lengths of several centimeters, we were able to assess the change of time in hormonal activity, with the closest hair to the scalp representing the most recent hormone accumulation [63,64].

Trained research assistants cut a small section of hair, containing around 50 to 100 strands, from the posterior vertex of the participant’s scalp following standardized hair sampling procedures [63]. If necessary, multiple small samples from the same region were collected to ensure that there was sufficient hair for analysis. The samples were preserved in foil and envelopes and labeled with the date and participant ID. Family members were also given the option to provide hair samples on site or follow instructions to cut them at home. The research team made efforts to accommodate different preferences for hair sample collection.

#### Surveys

##### Overview

Surveys containing standardized questionnaires were completed by parents and teachers either via paper and pencil or electronically via Qualtrics (Qualtrics International Inc), depending on preference and availability. Lead and assistant teachers completed surveys about themselves (self-report), and lead teachers completed surveys about each child in their classroom. Parents completed surveys about their children and a self-report survey about their perceived stress. Table 4 provides the list of survey questionnaires and scales collected at each time point and by respondents. Published scoring guidelines were used for all standard scales and questionnaires.

**Table 4 table4:** List of survey assessments and time points collected during the study.

Report type and category		Measure	Respondent	Time point
**Report on children**				
	Sociodemographic	Age, sex, race or ethnicity, disabilities, home language, and language proficiency	Parent and teacher	Before intervention
	Adversity	Adverse Childhood Experiences Questionnaire	Parent	Before intervention
	Social-emotional behavior	Children’s Behavior Questionnaire– very short form Strengths and Difficulties Questionnaire Open-ended questions^a^	Parent and teacher	Before intervention, after intervention, and follow-up
	Relationship and implicit bias	Student-Teacher Relationship Scale–short form Preschool expulsion risk measure Open-ended questionsa	Teacher	Before intervention, after intervention, and follow-up
**Self-report**				
	Sociodemographic	Age, sex, race or ethnicity, highest level of education achieved, household income, marital status, employment status, number of kids, and teachers’ role^b^	Parent and teacher	Before intervention
	Stress level	Perceived Stress Scale	Parent and teacher	Before intervention, after intervention, and follow-up
	Teachers’ changes	Teacher SEL^c^ Beliefs Scale Mindfulness in Teaching Scale	Teacher	Before intervention, after intervention, and follow-up

^a^These were also administered at the midintervention time point.

^b^Data collected only from teachers at follow-up.

^c^SEL: social-emotional learning.

##### Teacher Reports on the Children

Children who had parental consent were rated by lead teachers on preschool expulsion risk, student-teacher relationship quality, behaviors, and strengths and difficulties.

The Preschool Expulsion Risk Measure was used to measure implicit bias [65]. This 12-item scale included 4 subscales with 3 items each: classroom disruption, fear of accountability, hopelessness, and teacher stress. Items were rated on a 5-point Likert scale ranging from 1 (strongly disagree) to 5 (strongly agree), and mean scores were calculated. Higher scores represented a greater risk of expulsion.

The Student-Teacher Relationship Scale–short form was used to assess teachers’ perceived relationship quality with individual students [66]. This 15-item scale included 2 subscales: closeness (8 items) and conflict (7 items). Items were scored on a 5-point Likert scale ranging from 1 (definitely does not apply) to 5 (definitely applies). Mean scores were calculated with higher scores indicating more quality.

Open-ended questions were included in surveys at each time point. The teacher surveys included questions regarding expectations for each child in the MMP, what makes the job of teaching the child more or less enjoyable, and changes in the child’s behavior or typical behavior at school in general and during stressful situations over the course of the intervention. The teacher self-report surveys included questions related to feedback on having the research team visit their classrooms. Teachers were given the opportunity to comment about additional information they liked to share at the end of each survey.

##### Teacher and Parent Reports on the Children

The Children’s Behavior Questionnaire–very short form was administered to evaluate child temperament [67,68]. This 36-item questionnaire contained 3 subscales: surgency or extraversion, negative affectivity, and effortful control. The surgency or extraversion subscale included 12 items about a child’s sociability and activity level. Negative affectivity was a 12-item subscale that assessed the frequency of negative emotions, such as frustration. Effortful control was a 12-item subscale that focused on a child’s ability to regulate attention and manage impulses. Respondents were asked to read each statement and indicate the child’s reaction to that situation. Items were rated on a 7-point Likert scale ranging from 1 (extremely untrue) to 7 (extremely true). If a respondent had not observed the child in the situation, the response was left blank. Mean scores for each subscale were calculated with higher scores representing poor temperament.

The Strengths and Difficulties Questionnaire was a 25-item scale used to measure behavioral and emotional strengths and difficulties in children and young people [69]. This scale was divided into 5 subscales of 5 items each: hyperactivity, emotional symptoms, conduct problems, peer problems, and prosocial behavior. Each item was scored on a 3-point Likert scale ranging from 0 (not true) to 2 (certainly true). Sum scores were calculated for each of the 5 scales. A composite total difficulties score was generated by summing the scores for hyperactivity, emotional symptoms, conduct problems, and peer problems. Higher scores for hyperactivity, emotional symptoms, conduct problems, peer problems, and total difficulties denoted worse behavior, whereas higher prosocial scores represented better behavior.

##### Parent Reports on the Children

The Adverse Childhood Experiences Questionnaire was a 10-item measure used to identify traumatic events experienced during childhood, specifically involving abuse, neglect, and household dysfunction [70]. Each item prompted respondents to indicate whether specific events occurred in their child’s life, with answers scored as 1 (yes) and 0 (no). A total Adverse Childhood Experiences Questionnaire score was generated by summing the responses across all items. For this study, only 8 items were used; items regarding reportable events were removed. The minimum score was 0 and the maximum was 8, with a higher score indicating greater exposure to adverse childhood experiences.

The parent surveys about their child included open-ended questions regarding what makes parenting them more or less enjoyable and changes in the child’s behavior or typical behavior at home in general and during stressful situations that occurred over the course of the intervention. In the middle of programming, parents with children in the intervention group were asked whether their child shared anything with them about the program. At the end of classroom programming, parents were asked questions about using the calming corner kit at home. Parents were given the opportunity to comment about additional information they liked to share at the end of each survey.

##### Teacher and Parent Self-Reports

The Perceived Stress Scale was used to assess how different situations affect feelings and perceived stress over the past month in both teachers and parents [71]. This scale includes 10 items rated on a 5-point Likert scale ranging from 0 (never) to 4 (very often). Scores range from 0 to 40 with higher scores representing greater perceived stress.

The Mindfulness in Teaching Scale was used to assess teachers in the context of their teacher activities [72]. This 16-item scale is divided into 2 subscales: 8-item Intrapersonal Teacher Mindfulness and 8-item Interpersonal Teacher Mindfulness. Items are rated using a 5-point Likert scale, from 1 (never true) to 5 (always true). A total of 8 items were reverse coded such that subscales and total mindfulness score calculated sums had higher scores, indicating a greater level of mindful teaching.

The Teacher Social-Emotional Learning Beliefs Scale was a 12-item scale that assessed teachers’ beliefs about SEL [73,74]. This measure was divided into 3 subscales, each with 4 items: comfort with teaching SEL, commitment to learning about SEL, and school culture surrounding SEL. Respondents were asked to read each item and rate their agreement with each item for the past 4 weeks on a 5-point Likert scale from 1 (strongly disagree) to 5 (strongly agree). Composite scores for each subscale were generated by summing each item’s scores, with scores ranging from 4 to 20.

